### PROM (OQUA)

- The OQUA is a validated otological questionnaire and includes 34 questions, covering eight major types of ear complaints (earache, pressure in the ear, hearing loss, tinnitus, otorrhoea, itch, dizziness, and loss of taste). It measures the frequency and severity of these ear complaints and the impact on quality of life. The frequency of the ear complaints is expressed on a scale from 1-5, whereas the impact on quality of life is answered on a scale from 0-100. OQUA will be compared between treatment arms using a mixed model for repeated measures (MMRM) with fixed effects for treatment arm and timepoint (12 months, 36 months) and their two-way interaction. Analyses will be adjusted for OQUA at baseline. Primary inference will be based on the estimated mean difference at 36 months.

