**Main study parameters/endpoints:** Rates of recurrent or residual cholesteatoma are evaluated by diffusion-weighted magnetic resonance imaging (DW-MRI) and micro-otoscopy after approximately one, three and five years. If diffusion restriction is seen on DW-MRI and/or retraction of the tympanic membrane is seen during micro-otoscopy, suspicion for recurrent or residual disease will be recorded. To confirm the diagnosis and to determine whether the cholesteatoma is either recurrent or residual, we will analyse the tympanic membrane description at the beginning of the revision surgery. All other surgical outcome measures are recorded in the surgical report. Pure tone audiograms, including air and bone conduction, and speech recognition scores are evaluated pre- and postoperatively for each patient. The EQ-5D-5L, HUI-3, iMCQ and iPCQ questionnaires will be filled in once pre- and a two times postoperatively by every patient. The OQUA will be filled in once preoperatively and three times postoperatively. The direct health-care costs will be recorded for the sponsor centre and extrapolated for the whole trial.

**Nature and extent of the burden and risks associated with participation, benefit and group relatedness:** The burden patients will experience by participating in this study will be filling in the questionnaire multiple times. The surgery, along with the imaging procedures (CT and DW-MRI), audiometry and follow-up appointments, is part of standard care and takes place irrespective of participation in this study.

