All pre-operative measurements are part of standard care in the Netherlands and Belgium. Pre-operatively patients receive an audiometric exam, a physical examination of the ear, a CT-scan and fill in the patient-reported outcome measure (PROM). Follow-up will be planned at least at 6-18 weeks, at around 1 year and at around 3 years after surgery. It is important to note that conducting a CT scan and audiometry preoperatively as well as the DW-MRI's after 1 and 3 years are part of the standard care. In line with standard care, if there is a suspicion for recurrent or residual pathology (either clinically by micro-otoscopy or radiologically by DW-MRI) the treating physician will perform a revision surgery. If during revision surgery the suspicion is confirmed, the type of recidivism (residual or recurrent) is recorded and the follow-up of the patient ends. Data that is collected up until the point of detection of residual or recurrent disease will be used for analysis (this is not an exclusion criterium). If the suspicion is not confirmed (false-positive) then the patient will continue the follow-up as planned (unless a reconstructive procedure with the goal of improving hearing has been performed). During the three years of follow-up, patients should not undergo another type of ear surgery. If this is unavoidable, as judged by the treating physicians, the patient will be retrospectively excluded. In order to ensure that the same surgical data is collected in all participating centers, a standardized operation report will be written and shared by the sponsor (UMC Utrecht). This operation report will be recorded in the electronic patient dossier (with the exception of the information if obliteration was used or not) and transferred to Castor EDC. In Castor there will be a variable to also record if obliteration has taken place or not. The only methodology that is different to standard care is the randomization of the patients and the completion of the questionnaire. It is important to note that the technique used for the obliteration technique differs slightly between centers. The exact surgical technique will be described by the participating otologists and included in the description of the study, for example in a publication.

**Figure 1.** Flowchart of the study. *Standard care is indicated by \**[figure not shown]

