**Table 1. Study procedures**

| Measurement                                                                                               | Pre-operative (baseline) | Surgery Day 0 | Follow-up (post-operative) |                         |                         |                         |
|-----------------------------------------------------------------------------------------------------------|--------------------------|---------------|----------------------------|-------------------------|-------------------------|-------------------------|
|                                                                                                           |                          |               | 6-18 weeks                 | 12 months (+/- 1 month) | 36 months (+/- 1 month) | 60 months (+/- 1 month) |
| CT-scan                                                                                                   | X*                       |               |                            | (X)*                    | (X)*                    | (X)*                    |
| Audiometry                                                                                                | X*                       |               | X*                         | X*                      |                         |                         |
| Visit outpatient clinic and micro-otoscopy                                                                | X*                       |               | X*                         | X*                      | X*                      | X*                      |
| Inclusion                                                                                                 | X                        |               |                            |                         |                         |                         |
| Randomization                                                                                             | X                        |               |                            |                         |                         |                         |
| Surgery                                                                                                   |                          | X*            |                            |                         |                         |                         |

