### Hearing outcome

- For each patient the mean difference of the four frequencies (500,1000,2000,4000 Hz) between pre- and postoperative audiograms will be calculated to yield the air-bone gap. Hearing outcomes will be compared between the treatment arms using a mixed model for repeated measures (MMRM) with fixed effects for treatment arm and timepoint (6-18 weeks and 12 months) and their two-way interaction and a random effect for subject. Analyses will be adjusted for the hearing outcome at baseline. Primary inference for hearing outcomes will be based on the estimated mean difference at 12 months. If assumptions of normality of residuals is not met, transformations of the outcome will be considered or alternatively non-parametric tests Mann-Whitney U test will be used to compare the audiological data between the two groups (A,B) separately at 6-18 weeks and 12 months. Hearing results will be visualized using the Amsterdam Hearing Evaluation Plot (AHEP) (28). To illustrate the outcomes of the speech audiograms, a scatterplot will be made according to Stanford medicine. <https://hearingoutcomes.stanford.edu/>

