## **Economic evaluation**

- A cost utility analysis will be performed as described under the methods section.

The amount of missing data will be mentioned in the results. Missing data will be imputed using multiple imputation. All analyses will be performed on an intention-to-treat basis.

Additionally, dropout rates will be monitored, and any differential attrition between treatment arms will be appropriately accounted for in the statistical analysis.

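### The OQUA is collected at 6-18 weeks, but the OQUA model in section 8.2 uses only 12 and 36 months, so the early wave has no planned comparison (minor; free to correct)

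*Protocol*

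**What the plan says.** On collection, the Summary states: "The OQUA will be filled in once preoperatively and three times postoperatively". In Table 1 the postoperative columns are "6-18 weeks | 12 months (+/- 1 month) | 36 months (+/- 1 month) | 60 months (+/- 1 month"), and the OQUA row is marked at baseline and in the first three of these, not at 60 months.

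On analysis, the PROM (OQUA) item of section 8.2 compares the arms with a mixed model for repeated measures that has "fixed effects for treatment arm and timepoint (12 months, 36 months) and their two-way interaction". It adds "Analyses will be adjusted for OQUA at baseline" and "Primary inference will be based on the estimated mean difference at 36 months".

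The Hearing outcome item of the same section, by contrast, has "fixed effects for treatment arm and timepoint (6-18 weeks and 12 months").

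On missing data, the closing lines of section 8.2 say "Missing data will be imputed using multiple imputation", without naming the variables in the imputation model. They also promise that differential attrition will be accounted for. Section 3 says that when revision surgery confirms disease, "the type of recidivism (residual or recurrent) is recorded and the follow-up of the patient ends".

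**The concern.** Three postoperative waves are collected and two are modelled. Baseline has a role as covariate, so 6-18 weeks is the only OQUA wave without one. The protocol gives it no other analysis and no reason for leaving it out. This is not a detail left to a statistical analysis plan: section 8.2 fixes the time points, and they do not match the schedule.

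Two things are at stake. First, a repeated-measures model is valid under missing-at-random given the scores it contains. A patient who completes the 6-18-week OQUA and leaves before 12 months has no post-baseline score in the model as written, so loss that depends on early recovery is not conditioned on there. Second, Table 1 collects no other patient-reported instrument at 6-18 weeks. The early comparison of the two operations on earache, pressure, otorrhoea, dizziness and taste has no planned analysis, and one added after the data are seen would be post hoc.

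**Working it through.** **1. Schedule against model.**

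| OQUA wave | Collected (Table 1) | Role in the section 8.2 model |
|---|---|---|
| Baseline | yes | covariate |
| 6-18 weeks | yes | none stated |
| 12 months | yes | time point |
| 36 months | yes | time point, primary inference |

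**2. The plan's own figures.** The protocol gives no SD, power or precision for the OQUA. Its only attrition figure is the 10% margin in section 4.4: 160 / 0.9 = 177.8, so 178, or 89 per arm. This reproduces, and 89 per arm is used below.

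**3. Precision at 36 months.** Correlations and OQUA missingness are not in the protocol and are assumed. The variance of the baseline-adjusted 36-month difference was taken from the inverse of the model's information matrix, with and without the 6-18-week score, for monotone loss and known covariance. Correlations are 0.4, 0.6 and 0.8 between any two waves including baseline, either constant (CS) or decaying by wave (AR(1)). Reduction in standard error from adding the wave:

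| Missing at 12 / 36 months | CS 0.4, 0.6, 0.8 | AR(1) 0.4, 0.6, 0.8 |
|---|---|---|
| 0% / 0% | 0, 0, 0 | 0, 0, 0 |
| 5% / 10% | 0.31%, 0.51%, 0.68% | 0.05%, 0.21%, 0.49% |
| 10% / 30% | 0.84%, 1.31%, 1.70% | 0.09%, 0.37%, 0.88% |
| 15% / 40% | 1.13%, 1.77%, 2.32% | 0.12%, 0.51%, 1.25% |

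If 0.4-0.8 is instead the correlation among postoperative scores after adjustment for baseline, the 5% / 10% row becomes 0.57%, 1.12%, 1.78% (CS) and 0.06%, 0.31%, 1.01% (AR(1)). Over both readings, the range near the planned attrition is roughly 0.1-2%.

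**4. Upper bound.** If every patient missing at 36 months left between 6-18 weeks and 12 months, the variance ratio is 1 - rho^2 x m. Here rho is the correlation between the early and 36-month scores given baseline, and m is the fraction missing.

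- rho = 0.4, m = 0.10: 1 - 0.16 x 0.10 = 0.984; square root 0.992; standard error 0.8% lower.
- rho = 0.8, m = 0.10: 1 - 0.64 x 0.10 = 0.936; square root 0.967; standard error 3.3% lower.

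This is a ceiling. For patients lost after 12 months, the 12-month score is already in the model, and the early score adds only what that score does not carry.

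**5. Bias.** In a simulation of one arm (400,000 patients, unit SD), the log-odds of loss before 12 months were -2.1 + 1.0 x the early score, so about 14% were lost. The bias of the 36-month mean adjusted for baseline only was -0.031 (CS 0.4), -0.032 (CS 0.6), -0.032 (AR(1) 0.6) and -0.021 SD (CS 0.8). With the early score added it was within 0.002 SD of zero in all four.

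**The case against.** The strongest reply is that section 8.2 provides for multiple imputation and for differential attrition. The early OQUA can serve as an auxiliary variable, and imputation variables are commonly settled in a statistical analysis plan. This stands in part. A reader might infer that a patient with only the 6-18-week score contributes nothing after baseline to the analysis. The protocol does not support that: it is true of the model as written, but imputation could recover part of the information. Whether it will is left open. Imputation would in any case not give the 6-18-week comparison a planned analysis.

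A second reply is that inference at 36 months reflects a legitimate interest in lasting quality of life, and that hearing has only two postoperative waves, so its model needs the early one. Both are fair. The contrast with the hearing model shows that the early visit is treated as analysable. It does not prove an error in the OQUA model.

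Third, patients whose follow-up ends at confirmed disease should mostly do so at or after the 12-month visit, when the first scheduled DW-MRI takes place, so their 12-month OQUA would usually be in the model. This stands, and it limits the group concerned mainly to patients who drop out early.

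A reader might also infer a material loss of power or a threat to the trial's main result. Neither follows. The gain in standard error is small, the OQUA is a secondary outcome with no power claim, and the recidivism analysis does not use it. Nor does the protocol forbid reporting the early scores; it only plans no comparison of them.

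**Conclusion.** The mismatch is confirmed: three postoperative OQUA waves are collected, two are modelled, and the 6-18-week wave has neither a planned comparison nor a stated reason for omission. The consequence for the 36-month estimate is small. It is nil with complete data, roughly 0.1-2% in standard error near 10% missing, and more only with heavy loss before 12 months. The bias of about 0.02-0.03 SD arises only if early loss in one arm depends on the early score and imputation does not use that score. All these sizes rest on assumed correlations and missingness. The more practical consequence is the unplanned early comparison. This is a minor point on a secondary outcome, and the primary endpoint and its sample size are unaffected.

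**What to change.** In the PROM (OQUA) item of section 8.2, list the time points as 6-18 weeks, 12 months and 36 months, with the treatment-by-time interaction. Keep the adjustment for baseline and the primary inference at 36 months. Report the 6-18-week and 12-month differences from the same model as supportive.

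If the wave is left out on purpose, state the reason and say whether it enters the imputation model.

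The cost is one phrase, with no new data and no change to the OQUA contrast. It should be done before outcome data are examined.

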## SUMMARY

**Rationale:** The mainstay of cholesteatoma treatment is surgery with effective and safe removal of the disease as the principal goal. New techniques find their way in the international otologic community by proving lower recurrent and residual disease rates compared to the conventional techniques. One newly implemented and previously described technique is the obliteration technique of the mastoid. Although this approach has become more popular in recent years, high-quality evidence is missing.

**Objective:** The primary aim of this study is to investigate whether a canal wall up (CWU) tympanomastoidectomy with obliteration of the mastoid and paratympanic or epitympanic spaces reduces cholesteatoma recurrence and residual rates compared to the same approach without obliteration. Secondly, hearing outcomes after both surgical techniques are compared to investigate whether one of the two results in superior postoperative hearing. The quality of life will be measured using the Otology Questionnaire Amsterdam (OQUA). The economic evaluation will involve collecting the EQ-5D-5L, HUI-3, iPCQ and iMCQ questionnaires as well as direct intervention costs from the sponsoring centre.

**Study design:** The proposed study is a single-blind randomized controlled trial. One hundred seventy-eight patients will be included. Patients are randomized into one of two groups in an equal 1:1 allocation ratio. The randomization will be centre-stratified and a 4,6,8 block randomization will be used.

**Study population:** Patients above the age of 18 who undergo a CWU approach for removal of cholesteatoma in one of the participating centres.

**Intervention (if applicable):** Group A will undergo a CWU approach without obliteration and group B a CWU approach with obliteration.

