## 6.2 Randomisation, blinding and treatment allocation

If they sign the informed consent form they will be randomly allocated to one of the two treatment groups (A or B) using the Randomization Tool in Castor. Patients will be randomly assigned to one of the two study groups (A or B). A website randomisation program built within Castor will be used for the randomization. After informed consent, patients will be randomized. This is a single blind study, meaning that only participants are blinded for the treatment allocation. The surgeons cannot be blinded, as they will know which procedure they performed. The surgeon will not write down which procedure the patient received in the surgical report or in the letter to the general practitioner. It will only be recorded in Castor and in the RFS map. De blinding (single-sided) will only be lifted if it is in the interest of the safety of the participant. De participant and/or general practitioner can request this from the treating physician (ENT-surgeon) who performed the surgery. The ENT-surgeon will decide if lifting of the blinding is necessary and inform the researcher about this event. Only in case of medical emergency and in absence of the treating physician, other medical specialists can lift the blinding by checking the placement of the patient in the RFS map. All medical specialists have access to the RFS map with information of the participants where an inclusion table with randomization is stored. This way it is possible to lift blinding 24 hours a day.

Stratification will be used to distribute the two groups as evenly as possible between the participating centres. Patients are randomized into one of two groups in an equal 1:1 allocation ratio. A 4,6,8 block randomization will be used.

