### **8.1 Primary study parameter(s)**

The data of our primary outcome are quantitative and will be presented as frequencies and proportions. To compare the difference in recidivism (recurrent and residual disease) at 12, 36 and 60 months between both surgical groups the Chi-squared test or Fisher's exact test will be used. The relative risk (RR) and absolute risk difference (RD) will be calculated as effect sizes using a generalized linear model for binomial outcome with a log-link (for RR) and identity link (RD). The primary analysis will be adjusted for site by including centre as covariate in a logistic regression model with treatment arm as the main predictor. All effect sizes will be accompanied by 95% confidence intervals. To graphically demonstrate the rates of recidivism, recurrent and residual disease over the follow-up time, a Kaplan-Meier analysis will also be performed and survival curves will be constructed. Multiple imputation will be used to deal with missing

outcomes. A 20% difference is defined as the threshold for clinical relevance and will be consistently applied in both clinical effectiveness analyses and the health economic evaluation.

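### The OQUA and hearing models in section 8.2 leave out centre, the stratification factor, so their standard errors may be slightly too wide

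*Protocol*

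**What the plan says.** **Randomisation.** The protocol summary states: "The randomization will be centre-stratified and a 4,6,8 block randomization will be used". Section 6.2 repeats this: "Stratification will be used to distribute the two groups as evenly as possible between the participating centres". Allocation is equal: "Patients are randomized into one of two groups in an equal 1:1 allocation ratio".

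**Primary endpoint (section 8.1).** "The primary analysis will be adjusted for site by including centre as covariate in a logistic regression model", with treatment arm as the main predictor.

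**Hearing (section 8.2).** A mixed model for repeated measures "with fixed effects for treatment arm and timepoint (6-18 weeks and 12 months) and their two-way interaction and a random effect for subject". The covariate is the baseline value: "Analyses will be adjusted for the hearing outcome at baseline". If normality of residuals fails, the plan is to transform the outcome or to use a Mann-Whitney U test at each timepoint.

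**OQUA (section 8.2).** A mixed model for repeated measures "with fixed effects for treatment arm and timepoint (12 months, 36 months) and their two-way interaction". The covariate is again the baseline value: "Analyses will be adjusted for OQUA at baseline".

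Centre is in neither model of section 8.2 and is not mentioned for the rank test. No sentence in section 8 extends the centre adjustment to the secondary outcomes.

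**The concern.** Blocked randomisation within centres keeps the arms nearly balanced in each centre. Differences between centres in the general level of the outcome therefore largely cancel in the comparison of arms, and the true sampling variance of the arm difference is smaller for it. A model without centre does not know this. It counts the between-centre variation as residual or between-subject variation, and so reports a standard error larger than the true one. The random subject effect in the hearing model does not help, because it simply absorbs the centre variation.

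What is at stake is the width of the reported intervals and some power for hearing and OQUA. The sample size in section 4.4 is set for recidivism only, so the protocol shows no power for these outcomes, and imprecision that can be avoided at no cost is worth removing.

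**Working it through.** **Inputs from the protocol.** 1:1 allocation, stratified by centre, blocks of 4, 6 and 8 (Summary, section 6.2). 80 evaluable patients per arm, 160 in all (section 4.4). Two-sided alpha 0.05.

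**Inputs that the protocol does not give (assumed).** The share of outcome variance due to centre after baseline adjustment (ICC), taken as 0 to 0.20. The number of centres, taken as 6, 8 or 10 of equal size. An effect of 0.45 SD for the power check, where SD is the standard deviation left after baseline adjustment.

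**The plan's own figure.** Section 8.2 states no figure for OQUA or hearing. The section 4.4 calculation for the primary endpoint reproduces: exact enumeration of the pooled Z test with 80 per arm, 0.20 against 0.40, gives power 0.8009 and actual alpha 0.0472 (at a common rate of 0.40), and 160/0.9 = 177.8, rounded up to 178. It serves here only to supply the 160 patients.

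**Step 1: excess in the standard error.** With arms balanced within centres,

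SE without centre / SE with centre = 1/√(1 − ICC)

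actual two-sided alpha without centre = 2 × [1 − Φ(1.96/√(1 − ICC))]

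| Assumed ICC | SE ratio | Actual alpha without centre |
|---|---|---|
| 0 | 1.000 | 0.050 |
| 0.02 | 1.010 | 0.048 |
| 0.05 | 1.026 | 0.044 |
| 0.10 | 1.054 | 0.039 |
| 0.20 | 1.118 | 0.028 |

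**Step 2: simulation under no effect.** 160 patients, permuted blocks of 4, 6 and 8 within 6 centres, a baseline-adjusted linear model at one timepoint, complete data, 4000 runs per setting.

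| ICC | Mean reported SE, no centre | True SE, no centre | Rejection rate, no centre | Rejection rate, with centre |
|---|---|---|---|---|
| 0 | 0.158 | 0.158 | 0.051 | 0.049 |
| 0.10 | 0.158 | 0.152 | 0.040 | 0.052 |
| 0.20 | 0.159 | 0.141 | 0.026 | 0.047 |

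At ICC 0.10 the reported SE exceeds the true one by 0.1583/0.1517 = 1.044, a little less than the formula's 1.054, because incomplete blocks leave some imbalance and because of simulation error. Against the model with centre the ratio is 0.1583/0.1501 = 1.055. At ICC 0.02 the expected 1% excess is too small to show above simulation error.

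**Step 3: power.** Simulated with 8 centres and a 0.45 SD effect:

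| ICC | Power without centre | Power with centre | Difference (points) |
|---|---|---|---|
| 0 | 0.813 | 0.810 | none beyond simulation error |
| 0.05 | 0.805 | 0.818 | 1.3 |
| 0.10 | 0.817 | 0.844 | 2.7 |
| 0.20 | 0.835 | 0.889 | 5.4 |

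A check by formula at ICC 0.10: the SE reported without centre is 2/√160 = 0.1581, and the true SE is 0.1581 × √0.90 = 0.150. Power with centre is Φ(0.45/0.150 − 1.96) = Φ(1.04) = 0.851. Power without centre is Φ((0.45 − 1.96 × 0.1581)/0.150) = Φ(0.93) = 0.825. The difference is 2.6 points, in line with the simulation.

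**The case against.** **This belongs in the statistical analysis plan.** The covariates of secondary models are often settled there, and that plan is not shown. Section 8.1 commits to centre only for the primary analysis, so its absence from 8.2 contradicts nothing. That is fair as far as it goes: this is not an inconsistency. But section 8.2 does not leave the models open. It names the fixed effects, the baseline covariate and the timepoint for inference. An analysis that follows this text omits centre.

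**Nothing shows that centre matters for these outcomes.** This stands. A reader might infer centre effects from the remark in section 3 that the obliteration technique varies a little between centres. That remark is weak evidence. It concerns the obliteration arm only, so it points more to a treatment effect that varies by centre than to a shift common to both arms, and only a common shift is what the formula covers. Section 5.1 allows several obliteration materials but does not say that they vary by centre.

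**The loss might be read as a loss of patients.** A reader might take an ICC of 0.10 as equal to losing 10% of the patients. That confuses the reported standard error with the real precision of the estimate, since stratification already removes most of the centre variation from the estimate. Losing 10% of the patients from a power of 0.844 would give Φ((1.96 + 1.01) × √0.9 − 1.96) = 0.80, a loss of about 4 points, against 2.7 in the simulation.

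**Section 8.1 is not a uniform standard.** This also stands. Centre is stated there for the logistic model. The chi-squared or Fisher test and the models for relative risk and risk difference are described without it.

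**Conclusion.** The point holds as a small, conditional loss of efficiency. If centre predicts OQUA or hearing after baseline adjustment, the models as written report standard errors about 1% to 5% too wide for assumed ICCs of 0.02 to 0.10 (about 12% at 0.20, none at 0). Under the assumed effect and 8 centres, that costs about 1 to 3 percentage points of power at ICC 0.05 to 0.10. The omission itself is certain from the text. Its size is not, because the protocol gives neither the ICC nor the number of centres, and the simulation used a single timepoint, complete data and centres of equal size.

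A reader might infer that the secondary results would be invalid. They would not: the estimates are unbiased, and the error in the tests is on the conservative side. This is an improvement worth making, not a defect that threatens a conclusion.

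**What to change.** In section 8.2, add centre as a covariate to the OQUA model and to the hearing model, in line with the logistic model in section 8.1. For the hearing fallback, replace the plain Mann-Whitney test with a rank test stratified by centre. Make the change before outcome data are analysed by arm, so that the choice of covariate cannot be seen as made after the fact.

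The cost is one term in each of two models and a few degrees of freedom (one fewer than the number of centres). In the simulation with ICC 0, including centre left the standard error practically unchanged (0.1582 without, 0.1583 with, for 6 centres). No new data are needed, since centre is already recorded for the randomisation.
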